## Project Summary

[The summary, within a word limit of 300, should be stand alone and be fully understandable.]

Principal Investigator: [name] [name]

Research Protocol Title: Tolerability and Acceptability of Fibersol-2 (Resistant Maltodextrin) in healthy and diarrheal children followed by a randomized clinical trial to evaluate the efficacy of Fibersol-2 in diarrheal children 1-3 years old

Background (brief):

a. **Burden:** Dietary fibre, a non-digestible carbohydrate, has been used in decades for the beneficial effect on health with physiological importance because such compounds have low energy values. These indigestible carbohydrates generally reach the large intestine undigested and unabsorbed, they are often used in many functional and/or low-calorie food and beverages. Although, dietary fibre has a lot of benefit even in Europe and USA the consumption level is only 50-60% of the recommended level due to increased consumption of processed and pre-cooked food. Researchers have stated that dietary fibre especially digestive-resistant maltodextrin has innumerable beneficial effects on human health, such as improving intestinal regularity by increasing faecal bulk, stimulating peristalsis and shortening gastrointestinal transit time. Resistant maltodextrin (Fibersol-2) is a low viscosity, water-soluble, indigestible dextrin produced by the treatment of cornstarch with acid, enzymes, and heat. Resistant maltodextrin also have prebiotic activity. Prebiotic beneficially affects the host by stimulating the growth or activity of specific species of large bowel bacteria, including *Bifidobacterium* and *Lactobacillus*, thought to improve host health. In 1990, Ohkuma et al. showed the results of changing pattern of microbial flora caused by administration of resistant maltodextrin. Other beneficial physiological effect of resistant maltodextrin as prebiotic has been mentioned by several researchers, such as the effect on attenuating postprandial blood glucose levels, improving glucose and lipid metabolism, and preventing obesity. Hypothetically, resistant maltodextrin as prebiotic has been assumed to have the effect on mucosal immune response of the intestine.

b. **Knowledge gap:** Dietary fibre, a non-digestible carbohydrate, has been used in decades for the beneficial effect of health with physiological importance. Although dietary fibre has a lot of benefit even in Europe and USA the consumption level is only 50-60% of the recommended level due to increased consumption of processed and pre-cooked food. Non-digestible maltodextrin as water soluble dietary fibre with relatively low molecular weight and widely acceptable to all kind of foods and beverages can really solve the problem. Researchers have stated that dietary fibre especially digestive-resistant maltodextrin has innumerable beneficial effects on human health, such as improving intestinal regularity by increasing faecal bulk, stimulating peristalsis and shortening gastrointestinal transit time. As a prebiotic, almost half of resistant maltodextrin reach the large intestine and is fermented by intestinal flora. In 1990, Ohkuma et al. showed the result of changing pattern of microbial flora caused by administration of resistant maltodextrin. Other beneficial physiological effect of resistant maltodextrin as prebiotic has been mentioned by several researchers, such as the effect on attenuating postprandial blood glucose levels, improving glucose and lipid metabolism, and preventing obesity. In developing countries most of the diarrheal episodes occur during the first two years of life and till date antibiotics have been found to have no role in over seventy five percent of young childhood diarrhoea. Toddler's diarrhoea which affects children aged 6 to 60 months is known as chronic nonspecific diarrhoea of childhood. The stool is frequently watery or loose and may have food particles in it. Despite the diarrhoea, the child continues to grow and gain weight, remains active and has a normal appetite. Infections due to *Cryptosporidium*, *Giardia*, and *Clostridium difficile* can cause chronic diarrhoea in children. Other than infectious aetiologies these children may suffer from lactose intolerance, malabsorption, celiac disease, and less commonly

inflammatory bowel disease. Additionally, these episodes may have typical dietary and clinical history. Treatment for these episodes has been suggested to be normalization of feeding patterns according to the “four Fs”: Fat, Fibre, Fluid, and Fruit juice. Due to lack of evidence based studies regarding role of fibres in small apparently healthy children of Bangladesh, we anticipate to determine the safety, tolerability and acceptability of Fibersol-2 among children 1-3 years old.

**Relevance:**The beneficial effects of resistant maltodextrin are well known in developed countries; however, data are lacking in developing countries. Thus, it has become imperative to know its safety, tolerability and acceptability in small children with or without diarrhea in developing countries such as in Bangladesh. The present clinical trial will find out the safety, tolerability and acceptability of resistant maltodextrin in small children especially those 1-3 years old.

**Hypothesis (if any):**The resistant maltodextrin as a prebiotic is hypothesized to be safe, well tolerated and accepted in small children especially from 1-3 years old.

**Objectives:**The objectives of the present study are to assess the digestive tolerability of the Fibersol-2 in children which includes abdominal pain, rumbling, bloating, flatulence, and stool consistency. Additionally, the study will examine whether Fibersol-2 and ORS can reduce duration of watery diarrhea and stool output in children 1-3 years.

**Methods:** We are proposing to conduct an exploratory study to understand the digestive tolerability of resistant maltodextrin (Fibersol-2) in young healthy children aged 1-3 years. Additionally, we propose to conduct a placebo-controlled, randomized, double blind clinical trial to examine whether Fibersol-2 with ORS can reduce the duration of diarrhea and stool output in children of 1-3 years old.

**Outcome measures/variables:**

Main outcome measures will be; duration of diarrhoea, proportion of patients recovered within 72 hours, and daily stool output.

## Description of the Research Project

### Hypothesis to be tested:

In a hypothesis testing research proposal, briefly mention the hypothesis to be tested and provide the scientific basis of the hypothesis, critically examining the observations leading to the formulation of the hypothesis.

Does this research proposal involve testing of hypothesis: ☐ No ☒ Yes (describe below)

The resistant maltodextrin as prebiotic is assumed to be safe, well tolerated and accepted in small children especially from 1-3 years old.

### Specific Objectives:

Describe the specific objectives of the proposed study. State the specific parameters, gender aspects, biological functions, rates, and processes that will be assessed by specific methods.

The objectives of the present study are to assess the digestive tolerability of the Fibersol-2 in children which includes abdominal pain, rumbling, bloating, flatulence, and stool consistency. Additionally, the study will examine whether Fibersol-2 and ORS can reduce duration of watery diarrhea and stool output in children 1-3 years.

### Background of the Project including Preliminary Observations:

Provide scientific validity of the hypothesis based on background information of the proposed study and discuss previous works on the research topic, including information on sex, gender and diversity (ethnicity, SES) by citing specific references. Critically analyze available knowledge and discuss the questions and gaps in the knowledge that need to be filled to achieve the proposed aims. If there is no sufficient information on the subject, indicate the need to develop new knowledge.

### Introduction:

Dietary fibre, a non-digestible carbohydrate, has been used in decades for the beneficial effect on health with physiological importance because such compounds have low energy values. These indigestible carbohydrates generally reach the large intestine undigested and unabsorbed, they are often used in many functional and/or low-calorie food and beverages[1-5]. Although dietary fibre has a lot of benefit even in Europe and USA the consumption level is only 50-60% of the recommended level due to increased consumption of processed and pre-cooked food[6, 7]. Non-digestible maltodextrin as water soluble dietary fibre with relatively low molecular weight and widely acceptable to all kind of foods and beverages can really solve the problem. Researchers have stated that dietary fibre especially digestive-resistant maltodextrin has innumerable beneficial effects on human health, such as improving intestinal regularity by increasing faecal bulk, stimulating peristalsis and shortening gastrointestinal transit time. Resistant maltodextrin (Fibersol-2) is a low viscosity, water-soluble, indigestible dextrin produced by the treatment of cornstarch with acid, enzymes, and heat.

Resistant maltodextrin also have prebiotic activity [8-10]. Prebiotic beneficially affects the host by stimulating the growth or activity of specific species of large bowel bacteria, including *Bifidobacterium* and *Lactobacillus*, thought to improve host health. Prebiotics are known to result in a decrease in pathogenic bacteria, such as *Clostridium perfringens*. Other than that prebiotics by decreasing pH cause increased production of short chain fatty acid(SCFA) and result in increased competition for nutrients. As a prebiotic, almost half of resistant maltodextrin reach the large intestine and is fermented by intestinal flora [8, 11-13]. In 1990, Ohkuma et al. showed the results of changing pattern of microbial flora caused by administration of resistant maltodextrin. Other beneficial physiological effect of resistant maltodextrin as prebiotic has been mentioned by several researchers, such as the effect on attenuating postprandial blood glucose levels, improving glucose and lipid metabolism, and preventing obesity. Hypothetically, resistant maltodextrin as prebiotic has been assumed to have the effect on mucosal immune response of the intestine. In recent years, low-

molecular-weight water-soluble dietary fibres like maltodextrin have been hypothesized to induce gastrointestinal symptoms, including osmotic diarrhea. One study reported that a 5-10 g single dose of inulin can cause abdominal flatulence in 42-50% of subjects, and diarrhoea in some cases. A number of previous studies conducted in Bangladesh and other parts of the world suggested that partially hydrolyzed guar gum (PHGG) substantially reduced the duration of diarrhea and modestly decreased stool output in acute non-cholera diarrhea in young children, indicating its potential as a new anti-diarrheal therapy for acute diarrhea in children [4, 14-16]. The evidences showed that PHGG with added oral rehydration solution enhanced early recovery of acute diarrhoea in severely malnourished children in terms of reducing the duration of diarrhoea and stool output. Similar results were also reported when PHGG was used with ORS in the treatment of acute diarrhoea in non-severely malnourished children [14].

Although diet rich in fibre is widely recommended but efficacy of fibre supplements has not been tested sufficiently in children. One study with WHO-ORS containing partially hydrolyzed guar gum (PHGG) and another PHGG supplemented comminute chicken diet have reported to reduce diarrhea duration and stool output in children with acute and persistent diarrhea, respectively. PHGG is a soluble fibre and added PHGG in the ORS or diet escapes digestion in the small intestine and enter into the colon where the fibres are expected to be fermented by colonic bacteria producing SCFAs. SCFAs will stimulate sodium and water absorption in the colon leading to early recovery from diarrhea [17].

The viscosity of resistant maltodextrin is very clear and stable and does not become cloudy or show signs of any precipitation when kept for long periods of time. It also has very good anti-acid properties and can be cooked and sterilized at high temperature in food applications due to its stability in heat processes [9].

According to a systematic review, children admitted to hospital with dehydration associated with diarrhea, reduced osmolarity rehydration solution with diarrhea is associated with reduced need for unscheduled intravenous infusions, lower stool volume, and less vomiting compared with standard WHO rehydration solution. Children with acute diarrhea, therefore, may benefit from a reduced osmolarity ORS solution [18-21].

Dietary fibres can act by changing the nature of the contents of the gastrointestinal tract and by changing how other nutrients and chemicals are absorbed [22]. Advantages of consuming fibre are the production of healthful compounds during fermentation, increased bulk of stool, softening of stool, shortening of transit time through the intestinal tract, blocking of intestinal mucosal adherence, translocation of potentially pathogenic bacteria, and modulation of intestinal inflammation [23-27]. Based on literature review we are hypothesizing that resistant maltodextrin, a water-soluble, nonviscous and highly digestion-resistant maltodextrin is digestively tolerable and may not cause gastrointestinal symptoms including diarrhea in young healthy children. Additionally, it is hypothesized that resistant maltodextrin with ORS will be efficacious in the treatment of watery diarrhea in young children.

The objectives of the present study are to assess the digestive tolerability of the resistant maltodextrin in children which includes abdominal pain, rumbling, bloating, flatulence, and stool consistency. Additionally, the study will examine whether resistant maltodextrin and ORS can reduce duration of watery diarrhea and stool output in children 1-3 years.

It is a water-soluble dietary fiber (digestion resistant dextrin) which can easily be taken every day. It easily gets dissolved in water without changing its smell and taste at all. It can also be dissolved in any drink that one likes. Resistant maltodextrin contains 90% dietary fiber (dry solid base) which helps reduce absorption of sugar and fat so that the rise of blood sugar level and blood RLP-

cholesterol level after meal would be low. Adults are advised to have one packet (as dietary fiber 5g) per meal. Three packets per day are standard. It is advised to dissolve the packet in any drink and have that with meal.

In our study fibersol-2 (resistant maltodextrin) will be given to the study participants twice daily preferably in the morning and at evening with 50 ml of water for study children; but in case of diarrheal children in the proposed RCT we will use Fibersol-2 also with water because it is water-soluble dietary fibre dissolve in 50 ml of water without changing its smell and taste. We will evaluate two presumptive doses of Fibersol-2 in phase 1 to understand the better tolerability and acceptability of one of the doses of Fibersol-2 in healthy as well as diarrheal children and the suitable dose will be used for the clinical trial in diarrheal children.

An experienced researcher at icddr, b, not involved in the study, will prepare the randomization list using the randomization table. The name of random allocation will be indicated on a slip of paper, kept inside the sealed envelope. The sealed envelopes will be supplied to the researcher to supply the intervention package. The children with no dehydration or some dehydration will be randomized immediately after admission.

## Research Design and Methods

Describe the research design and methods and procedures to be used in achieving the specific aims of the research project. If applicable, mention the type of personal protective equipment (PPE), use of aerosol confinement, and the need for the use BSL2 or BSL3 laboratory for different part of the intended research in the methods. Define the study population with inclusion and exclusion criteria, the sampling design, list the important outcome and exposure variables, describe the data collection methods/tools, and include any follow-up plans if applicable. Justify the scientific validity of the methodological approach (biomedical, social, gender, or environmental).

Also, discuss the limitations and difficulties of the proposed procedures and sufficiently justify the use of them.

We are proposing to conduct an exploratory study to understand the digestive tolerability of resistant maltodextrin (Fibersol-2) in young healthy and diarrheal children aged 1-3 years for 30 children at home and 30 children at hospital in phase 1. Additionally, we propose to conduct a placebo-controlled, randomized, double blind clinical trial to examine whether Fibersol-2 with water can reduce the duration of diarrhea and stool output in children of 1-3 years old in the tertiary level hospital. If the child vomits out within 10 minutes of oral intake, we will give him again similar amount of fibersol-2 for consumption after an hour of rejection; if the child vomits again within 10 minutes of next intake, we will stop giving him fibersol-2 anymore. We will also assess the digestive tolerability of the study children. In addition to gathering information from hospital, our field research staff will visit the households of study children to collect information about their health status by administering field tested questionnaire.

Our study staff members will follow-up the study participants round the clock (24 hrs) during their hospital stay. To ensure the patient care they maintain a roster duty with staff members consisting 2 Project Research Physicians, 4 Study Nurse, 2 Field Research Assistants and 4 Field Organizer. Project physician will be responsible for consenting as well as all clinical assessment including the assessment of the diarrheal patients and provide treatment, besides these they will be given treatment for other illness if needed, our study nurses are responsible for recording vital signs and will feed the Fibersol-2 to the study participants in front of their legal guardians at hospital and community level with appropriate dose and time. They will also be closely monitoring the participants after oral intake of fibersol-2; if any adverse event is observed they will call the study physician immediately. Our Field Research assistant and Field Organizer will be screening the community control as well as will record other socio-demographic information and anthropometry as required. They will also assist the study nurse in monitoring the study participants at household level.

Flow chart of study design:

[figure not shown]

### *Study design of exploratory study*

We will conduct the study in two phases – in phase I the safety and tolerability issues will be examined among healthy **and diarrheal** children ( $n=30+30=60$ ), and if Fibersol-2 is found to be safe and tolerable, we will approach the DSMB to seek permission to extend the study for phase II as the clinical trial only in diarrheal children. The evaluable clinical signs include abdominal pain, rumbling, bloating, flatulence, and stool consistency.

### *Eligibility for assessing digestive tolerability*

Eligible age for the study: 1-3 years  
 Genders eligible for the study: Both  
 Include only healthy children: Yes

### *Eligibility criteria for the exploratory study*

Inclusion criteria for healthy children:

- (i) Healthy children, (ii) Aged between 1-3 years, and (iii) Received written consent from parents

Exclusion criteria:

- (i) History of food allergy, (ii) Antibiotic or any medication that impacts the gut transit during the two weeks before the study, (iii) Chronic gastrointestinal disease, (iv) Gastroenteritis in the two weeks before the study, (v) Constipation (less than 3 stools per week) or diarrhea (three or more than 3 stools per day), (vi) child in a situation and could interfere with the optimal participation to the study or constitute a particular risk of non-compliance, (vii) currently participating in another clinical trial, and (viii) Parents refused to give written consent.

Inclusion criteria for diarrheal children:

Eligible age for the study: 1-3 years  
 Genders eligible for the study: Both  
 Include only diarrheal children: Yes  
 and (iii) Received written consent from parents  
 Exclusion criteria:

(i) History of food allergy, (ii) Antibiotic or any medication that impacts the gut transit during the two weeks before the study, (iii) Chronic gastrointestinal disease, (iv) Gastroenteritis in the two weeks before the study, (v) Constipation (less than 3 stools per week) (vi) child in a situation and could interfere with the optimal participation to the study or constitute a particular risk of non-compliance, (vii) currently participating in another clinical trial, and (viii) Parents refused to give written consent.

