### *Methods for exploratory study*

Study arm: 2 arms study which consists of 15 healthy children in each arm with Fibersol-2 dosing 2.5 g twice daily and 5g twice daily respectively

1. Study group 1, 15 healthy children will receive Fibersol-2, 2.5g twice daily with 50 ml drinking water
2. Study group 2, 15 healthy children will receive Fibersol-2, 5g with 50 ml drinking water twice daily

Study arm: 2 arm study which consists of 15 diarrheal children in each arm with Fibersol-2 dosing 2.5 g twice daily and 5 g twice daily respectively

1. Study group 1, 15 diarrheal children will receive Fibersol-2, 2.5g twice daily with 50 ml drinking water
2. Study group 2, 15 diarrheal will receive Fibersol-2, 5g with 50 ml drinking water twice daily

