### *Eligibility criteria for the clinical efficacy trial*

#### Inclusion criteria:

(i) Children with acute watery diarrhea, 3 or more watery stool in any 24-hour period of <7 days duration with none or some dehydration (ii) Aged between 1-3 years, and (iii) Received written consent from parents

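### The phase I diarrhoeal cohort excludes recent gastroenteritis without exempting the episode that brings the child in

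*Protocol*

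**What the plan says.** Phase I has two cohorts of 30 children each, healthy and diarrhoeal, and each is split into two dose groups of 15. For the second cohort, Methods for exploratory study states: "Study arm: 2 arm study which consists of 15 diarrheal children in each arm with Fibersol-2 dosing 2.5 g twice daily".

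Under Eligibility criteria for the exploratory study, the diarrhoeal cohort is admitted on age, either sex, parental consent and "Include only diarrheal children: Yes". Its exclusions include "iii) Chronic gastrointestinal disease" and then "iv) Gastroenteritis in the two weeks before the study, (v) Constipation (less than 3 stools per week) (vi) child". In the healthy cohort's list the fifth item is longer: "v) Constipation (less than 3 stools per week) or diarrhea (three or more than 3 stools per day".

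The preceding section, Eligibility for assessing digestive tolerability, names no cohort and says "Include only healthy children: Yes".

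For the randomised trial the inclusion criterion is "Children with acute watery diarrhea, 3 or more watery stool in any 24-hour period of <7 days duration with none or some dehydration". The trial's exclusions do not mention recent gastroenteritis.

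Phase I serves two purposes. The Introduction says tolerability will be judged in healthy and diarrhoeal children and that "the suitable dose will be used for the clinical trial in diarrheal children". Study design of exploratory study makes the approach to the DSMB about phase II conditional on phase I showing safety and tolerability.

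**The concern.** The inclusion criterion and exclusion (iv) pull against each other. A child brought in with acute infective diarrhoea meets the first and, on the plain words, fails the second. Staff would have to choose between turning away typical cases and reading into (iv) an exemption that is not written.

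If they apply the words strictly, the diarrhoeal cohort shifts towards children whose diarrhoea is judged not to be gastroenteritis, which is not the population of the later trial. If they waive (iv) informally, children are enrolled against a written exclusion, and the data shown to the DSMB carry that question. In either case the cohort meant to show tolerability in diarrhoea becomes harder to interpret when the dose is chosen and phase II is requested.

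**Working it through.** No figure in the plan is in dispute, so the check compares the passages.

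**1. The two phase I exclusion lists.**

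| Item | Healthy cohort | Diarrhoeal cohort |
|---|---|---|
| (i) food allergy | excluded | excluded |
| (ii) antibiotic or gut-transit medication, prior two weeks | excluded | excluded |
| (iii) chronic gastrointestinal disease | excluded | excluded |
| (iv) gastroenteritis, prior two weeks | excluded | excluded, unchanged |
| (v) constipation | excluded | excluded |
| (v) current diarrhoea | excluded | removed |
| (vi) to (viii) participation risk, other trial, no consent | excluded | excluded |

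The only difference is that current diarrhoea was removed from item (v). Item (iv) has the same wording for both cohorts. In healthy children it is coherent. In children who must have diarrhoea it needs a qualifier, and none is given.

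**2. The time window.** Let d be the days from onset of the current episode to enrolment. The window in (iv) is 2 × 7 = 14 days. A trial-type episode has d < 7, so onset falls inside the window, with more than 14 − 7 = 7 days to spare. A longer episode that is still running overlaps the window too, whatever its onset. So if the current illness is gastroenteritis and began before enrolment, (iv) applies as worded.

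**3. Who could still qualify.** The Protocol does not define gastroenteritis. A child whose diarrhoea is attributed to another cause passes (iv), unless the cause is a chronic gastrointestinal disease, which (iii) excludes. The documents give no proportion for this group.

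**4. Children affected.** 15 + 15 = 30 of 30 + 30 = 60, or half of phase I.

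**5. Fit with the trial population.** The diarrhoeal cohort's criteria set no stool-count definition, duration limit or dehydration grade, and do not exclude bloody diarrhoea or severe disease. The trial's criteria address all of these. The trial text is not consistent on dehydration: its inclusion criterion allows none or some, the opening of Methods for clinical efficacy trial describes children with none, and the end of that section again allows none or some.

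**The case against.** The strongest reply is that (iv) can be read together with the inclusion criterion, as a bar on a separate, earlier episode. That would be a reasonable filter when new abdominal symptoms are being judged. Removing diarrhoea from (v) shows that the list was adapted, and keeping (iv) may have been deliberate. This is plausible, and the documents do not settle whether (iv) was kept on purpose or carried over. But the text does not state the earlier-episode meaning, and an exclusion criterion has to work as written.

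A reader might also infer several stronger points that the documents do not support:

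- **That almost no child with diarrhoea could enrol, or that every enrolment would be a deviation.** Gastroenteritis is undefined, no proportion is given, and under the earlier-episode reading there is no deviation at all.
- **That phase I explicitly targets acute diarrhoea.** Its criteria say only diarrhoeal. The link to acute cases comes from the use made of the result in the later trial.
- **That phase I is restricted to healthy children.** The healthy-only line stands directly before the healthy criteria, a parallel line exists for the diarrhoeal cohort, and the 30 + 30 design is stated repeatedly. It is an unlabelled header.
- **That the trial's criteria should replace the cohort's.** This would drop the exclusions for food allergy, recent medication and chronic disease, which are defensible when the outcomes are pain, bloating, flatulence and stool consistency. It would also import the unresolved dehydration wording. A tolerability cohort need not match the later trial in every criterion.

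It is also fair to say that the healthy cohort contributes to the dose choice, that the DSMB stands between the two phases, and that the trial's own eligibility criteria do not contain (iv). Randomisation and the efficacy comparison are therefore not directly affected.

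**Conclusion.** The point holds in a narrow form. For the phase I diarrhoeal cohort, inclusion and exclusion (iv) conflict as written, because (iv) does not exempt the presenting episode. Read literally, it bars children whose current diarrhoea is gastroenteritis, including those of the type the trial will enrol. It touches both diarrhoeal dose groups, 30 of 60 phase I children, whose results help to inform the dose and the request to open phase II.

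This rests on the plain wording of (iv) and on the assumption that much acute watery diarrhoea would be classed as gastroenteritis. The number of children lost cannot be derived from the documents, and the conflict does not depend on it. This is a conflict between stated criteria, and eligibility belongs in the protocol, so a statistical analysis plan would not resolve it.

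**What to change.** In Eligibility criteria for the exploratory study, reconcile the diarrhoeal cohort's inclusion criterion with exclusion (iv). Either state that (iv) refers to a separate, earlier episode and not the presenting one, or remove (iv) for this cohort. If the first option is taken, say how a separate episode is recognised.

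Label the block under Eligibility for assessing digestive tolerability as applying to the healthy cohort only.

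Check the cohort's definition of diarrhoea against the trial's eligibility and methods sections, reconcile the dehydration wording in those sections first, and record which differences are intended. The other tolerability exclusions need not be dropped.

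The cost is an eligibility wording amendment, with no extra children, visits or procedures. If diarrhoeal children have already been enrolled in phase I, the report should state how (iv) was applied to them.

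### The Phase I diarrhoeal cohort inherits the healthy-child exclusion for gastroenteritis in the past two weeks, with no exemption for the presenting episode

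*Protocol*

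**What the plan says.** Under Eligibility criteria for the exploratory study, the Protocol gives two Phase I lists, one for healthy children and one for children with diarrhoea. The diarrhoeal list opens with "Include only diarrheal children: Yes". Its exclusions then run, in part, "iv) Gastroenteritis in the two weeks before the study, (v) Constipation (less than 3 stools per week) (vi". In the healthy list the item after gastroenteritis reads "v) Constipation (less than 3 stools per week) or diarrhea (three or more than 3 stools per day", so the diarrhoea clause was taken out when the list was reused.

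Methods for exploratory study sets the size of the cohort: "2 arm study which consists of 15 diarrheal children in each arm". Research Design and Methods gives the settings: "young healthy and diarrheal children aged 1-3 years for 30 children at home and 30 children at hospital in phase 1".

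The efficacy trial has its own criteria. It enrols acute watery diarrhoea with "3 or more watery stool in any 24-hour period of <7 days duration", and its exclusion list has no gastroenteritis item.

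Phase I leads to Phase II in two ways. Study design of exploratory study makes the request to the DSMB to proceed depend on Phase I safety and tolerability. The dosing paragraph at the end of the Introduction says that, after two doses have been tried in healthy and diarrhoeal children, "the suitable dose will be used for the clinical trial in diarrheal children".

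**The concern.** An exclusion criterion should not catch the condition that makes a child a candidate. Acute infectious diarrhoea is, in ordinary usage, gastroenteritis. If it began before enrolment, the child has had gastroenteritis within the preceding two weeks. Taken at its word, the item therefore conflicts with the inclusion line above it.

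This cohort supplies the only Phase I evidence in children with diarrhoea. If some screeners apply the item to the current illness and others do not, the cohort's make-up will depend on who screened. It may also drift away from the children to whom the chosen dose will be given in the efficacy trial.

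**Working it through.** No arithmetic in the plan bears on this point, so the check is a comparison of the lists.

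**Step 1. Compare the exclusion items.**

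| Item | Phase I, healthy | Phase I, diarrhoeal | Efficacy trial |
|---|---|---|---|
| (i) Food allergy | yes | yes, unchanged | absent |
| (ii) Antibiotic or transit-altering drug, past two weeks | yes | yes, unchanged | absent |
| (iii) Chronic gastrointestinal disease | yes | yes, unchanged | absent |
| (iv) Gastroenteritis, past two weeks | yes | yes, unchanged | absent |
| (v) Constipation | yes, with current diarrhoea | constipation only | absent |
| (vi)–(viii) Compliance risk, other trial, consent refused | yes | yes, unchanged | present |

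Only item (v) was adapted in substance for children with diarrhoea. Items (iii) and (iv) stand together in both Phase I lists: "iii) Chronic gastrointestinal disease, (iv) Gastroenteritis in the two weeks before the study". I found no text elsewhere in the Protocol that limits (iv) to an earlier episode.

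**Step 2. Place the current episode in the window.** Take entry to the study as the reference point (an assumption, since the item does not define it), and let d be the time from onset of the current episode to entry. Item (iv) covers 0 < d ≤ 14 days. The efficacy trial's definition allows d < 7 days. Since 7 < 14, every episode of infectious origin that meets that definition and began before entry falls inside the window.

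**Step 3. Ask who remains eligible on the literal reading.** Item (iv) removes recent gastroenteritis and item (iii) removes chronic gastrointestinal disease. Diarrhoea that is neither is left. The Project Summary names non-infectious causes of diarrhoea in children, such as lactose intolerance and malabsorption. The Protocol does not say whether these count as chronic disease under (iii), and it does not define gastroenteritis. The Phase I inclusion criteria also do not require the diarrhoea to be acute, infectious or of any stated duration. The literal exclusion is therefore near-total at most, and the documents give no basis for a percentage.

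**Step 4. Size of the cohort concerned.** 2 dose groups × 15 = 30 children, which is 30 / 60 = 50% of Phase I.

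**Step 5. Look for related text.** Eligibility for assessing digestive tolerability restricts the tolerability assessment to healthy children, without qualification. That line conflicts with having a diarrhoeal cohort in Phase I at all, and it looks like another remnant of a healthy-only design.

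**The case against.** The best defence is that nobody would read the item this way. Removing the diarrhoea clause from (v) shows that the authors meant current diarrhoea to be acceptable. Beside an inclusion line calling for diarrhoeal children, (iv) reads naturally as a history item, like the medication item with the same two-week window. Staff would then apply it to an earlier, separate episode, and recruitment would proceed normally. I accept this as the likely intent. It does not settle the matter, because the text does not state it and the two readings give opposite decisions on the same child.

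The defence is also right about scope. The efficacy trial has its own eligibility list without this item, and the go-ahead and the dose choice draw on the 30 healthy children as well, for whom (iv) is coherent.

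A reader might infer more: that the rule empties the cohort, that recruitment must fail, or that every enrolled child with earlier onset will be an eligibility violation in data put before the DSMB. The documents do not support this. Emptying the cohort would require diarrhoeal to mean acute and infectious, and Phase I does not say so; the under-7-day definition belongs to the efficacy trial. The other two consequences follow only if the literal reading is the one in force, and they leave out the probable case in which staff apply the item to a prior episode. On the DSMB, the Protocol says only that permission to extend the study will be sought; it does not describe a data set to be submitted.

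**Conclusion.** The point holds as an internal inconsistency in the Phase I eligibility text. Item (iv) of the diarrhoeal list, as written, excludes children whose presenting illness is acute infectious diarrhoea that began before enrolment. This contradicts the cohort's inclusion line and shuts out the kind of child the efficacy trial will enrol.

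It concerns the 30 diarrhoeal children planned for Phase I. The effect on enrolment cannot be quantified, because it depends on how screeners read the item and on terms the Protocol leaves undefined. The conclusion assumes that gastroenteritis includes acute infectious diarrhoea and that the two weeks run back from study entry.

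The link to Phase II is indirect, through the go-ahead and the dose choice. The efficacy trial's eligibility criteria and its 46 per group are not affected. I rate this should-fix: a real ambiguity in a criterion, cheaply removed, but not a threat to the efficacy comparison itself.

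**What to change.** In the exclusion list for diarrhoeal children only, either delete item (iv) or limit it to an episode of gastroenteritis that is separate from, and earlier than, the presenting one. Keep the present wording for healthy children.

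In the same amendment, reconcile the healthy-only line under Eligibility for assessing digestive tolerability with the diarrhoeal cohort. Otherwise the Phase I eligibility text will still contradict itself.

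The cost is two short edits to the Protocol and a matching change to the screening form. No extra children, visits or measurements are needed, and the sample size does not change.
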